### Intervention

Health care aides will be trained to prompt residents to repeatedly stand up and sit down on four occasions during daily functional activities (twice on each of the day and evening shifts). The number of repetitions on each occasion will vary according to residents' ability and fatigue. The sit-to-stand activity is to be integrated into usual care routines such as when entering the dining room at mealtimes, while toileting, and on other occasions of regular activity. The timing and location will be at the discretion of the health care aide. Health care aides will be reminded that, as with their usual care activities, when a resident's condition deteriorates they should consult with the registered nurse or licensed practical nurse about the appropriateness of repeating the sit-to-stand activity.

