### Intervention group

Residents in the three intervention facilities will be exposed daily to the intervention for 6 months. This will enable an assessment of the effect of the intervention on residents' mobility over time and a preliminary assessment of the sustainability of the intervention. Their mobility, function in basic activities of daily living, and health-related quality of life will be measured at baseline, 3 months and 6 months.

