### Control group

Resident participants in the control facilities will receive usual care. The only change in their routine will be the measurement of mobility, function and health-related quality of life on three occasions as for residents in the intervention group. Health care aides may work in more than one unit in a facility thus intervention and control groups will be designated at the facility level rather than the unit level to avoid contamination of the control group. It is also possible that some health care aides may work in more than one facility. We will assess the extent of contamination of the control group at the end of the study by asking health care aides who work control facilities if they have ever encouraged residents in the control facilities to repeat sit-to-stands.

LTC facilities in the intervention group will be matched to the control group facilities on ownership model (public, private for-profit, voluntary not-for-profit) and size because quality of care and resident outcomes are associated with ownership models [49-54] and size [48,49,52]. To assess the comparability of the intervention and control facilities a research assistant will gather information about each facility by: a) interviewing managers to obtain information such as staff-to-resident ratios on each shift, availability of rehabilitation services and size of units; b) observing activity across both the day and evening shifts using a structured observation schedule; and c) measuring environments using two standardized instruments: the Alberta Context Tool and the Professional Environmental Assessment Protocol (PEAP). Drawing on data collected from the observations and data elicited during the manager interviews, total PEAP scores will be calculated immediately following each manager interview.

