### Outcomes

#### Mobility

The sit-to-stand action is a functional activity that has been incorporated into a number of mobility measures including the time to rise without using arms, time for 5 sit-to-stands, time for 10 sit-to-stands, and the number of sit-to-stands completed in 30 seconds. We have chosen to measure mobility using the number of sit-to-stands in 30 seconds because in the frail nursing home population many residents must use their arms to stand [10,38,47,48] and may be unable to complete more than one sit-to-stand. This mobility assessment will be completed by a research assistant using a stopwatch and standard armchair with a standard height of 42 cm. Residents will be instructed to stand up and sit down as many times as possible until they are asked to stop after 30 seconds. In a group of community-dwelling older adults aged 66 to 97 years [47], researchers found evidence for test-retest reliability, criterion validity (comparing the chair stand performance to a measure of lower body strength), and discriminant validity (comparing performance in different age and physical activity groups) with the 30-second sit-to-stand test.

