#### Adverse Events

Monitoring of adverse events in the intervention facilities will be compared with adverse events in the control facilities. We expect to see a reduced incidence of resident falls and related injuries in the intervention facilities. Likewise we expect to see a reduction in the injury of health care aides working in the intervention facilities. Resident safety is unlikely to be compromised given our pilot study experience and the experience of others in carrying out exercise interventions in a similar population [20,28,37,42,104,105]. Although the mobility intervention is expected to reduce residents' risk of falls by maintaining or improving their mobility, maintaining mobility extends the time that residents are at risk of a fall. We will monitor resident participants' falls monthly and compare these with their baseline pattern of falls three months prior to entering the study. In the event of a resident participant falling in one of the intervention facilities the principal investigator will decide in collaboration with the LTC facility manager whether or not that resident should remain in the study.

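### The post-fall decision in intervention facilities is worded as leaving the study rather than stopping the activity, which permits one-sided loss of outcomes

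*Protocol article*

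**What the plan says.** All references are to the protocol article.

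- **Adverse Events.** Falls of resident participants are tracked monthly, and "Monitoring of adverse events in the intervention facilities will be compared with adverse events in the control facilities". The action after a fall is set out for one arm: "In the event of a resident participant falling in one of the intervention facilities the principal investigator will decide", together with the manager of that facility, "whether or not that resident should remain in the study". No corresponding decision is described for control residents.
- **Intervention.** There is a separate route for reconsidering the activity itself. Aides are told that, if a resident deteriorates, "they should consult with the registered nurse or licensed practical nurse about the appropriateness of repeating the sit-to-stand activity".
- **Control group.** For control residents, "The only change in their routine will be the measurement of mobility, function and health-related quality of life on three occasions".
- **Intervention group and Schedule of Intervention.** In the intervention group, mobility, function and "health-related quality of life will be measured at baseline, 3 months and 6 months". Schedule of Intervention plans the two follow-up measurements for both groups and makes no exception for residents who fall.
- **Data Analysis.** Analysis is by intention-to-treat. The explanation attached to that term covers residents who move elsewhere and residents who die.

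**The concern.** Two different decisions can follow a fall. One is whether the resident should go on repeating sit-to-stands, which is a clinical question about the intervention. The other is whether the resident should go on being measured, which decides whether the data exist. The Adverse Events wording refers to the second. The Intervention section shows that the authors can word the first.

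Applied literally, the rule lets an investigator who knows the arm end follow-up for some intervention residents after a post-baseline event closely tied to mobility, with no counterpart in the control arm. The 3- and 6-month outcomes of those residents, and their later falls, would be missing. No analysis plan can recover them, and covariate adjustment does not reliably correct for loss of this kind. The study compares six facilities that were not randomised, so an avoidable asymmetry between arms should not be added.

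The direction is open. If the removed residents would have declined more than those who stay, the intervention looks better than it is. If they are residents who kept their mobility and so stayed exposed to falling, it looks worse. The protocol raises the second mechanism itself: "maintaining mobility extends the time that residents are at risk of a fall".

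**Working it through.** **Inputs from the Sample Size section.** Target difference 2 stands; SD 3.5; two-sided alpha 0.05; power 0.80; 60 residents recruited per group; 20% attrition over 6 months.

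**The plan's own figure.** n per group = 2 × (1.960 + 0.842)² × 3.5² / 2² = 48.07, rounded up to 49. This reproduces the stated 49. With 20% attrition, 60 × 0.8 = 48 per group complete.

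**Inputs not in the documents (assumed).** The share of residents who fall, the share of fallers removed, and the gap D in change from baseline between residents who stay and residents removed (D = change in stayers minus the change the removed would have shown).

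**Formula.** With f the share of the intervention arm removed before a visit, the full-arm mean change is (1 − f) × stayers + f × removed. Stayers minus full arm is therefore f × D, which is the bias in the group contrast. Other losses are ignored. A gap already present at baseline cancels in change from baseline; a gap in decline does not.

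**Middle case, 6 months.** 40% fall and a quarter of fallers are removed: f = 0.40 × 0.25 = 0.10, or 6 of 60.
- D = 1: bias 0.10 stands, which is 0.10/2 = 5% of the target and 0.10/3.5 = 0.03 SD.
- D = 2.5: bias 0.25 stands, which is 12.5% of the target and 0.07 SD.

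**Middle case, 3 months.** At a constant fall rate, 1 − (1 − 0.40)^0.5 = 0.225 have fallen by then. So f = 0.225 × 0.25 = 0.056, and the bias is 0.06 to 0.14 stands.

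**Range at 6 months.**

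| Assumption | f | D | Bias (stands) |
|---|---|---|---|
| 20% fall, 10% of fallers removed | 0.02 | 1 | 0.02 |
| Middle case | 0.10 | 1 to 2.5 | 0.10 to 0.25 |
| Removals use all planned attrition (12 of 60) | 0.20 | 1 to 2.5 | 0.20 to 0.50 |
| Gap wholly present at baseline | any | 0 | 0 |
| Removed residents would have done better | 0.10 | −1 | −0.10 |

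**Effect on the test, middle case.** With 48 per arm, SE = 3.5 × √(2/48) = 0.714; 3.5 is also the SD of change if the correlation with baseline is 0.5. If the true effect is zero, a bias of 0.10 gives a two-sided type I error of 0.052 and a bias of 0.25 gives 0.064. This ignores clustering by facility; any positive intraclass correlation enlarges the SE and reduces the inflation.

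**The case against.** The strongest case on the other side is that this is one loose phrase in the safety paragraph of a condensed article. Schedule of Intervention plans measurement at 3 and 6 months for both groups without exception. A team that keeps even residents who relocate or die in its analysis probably does not mean to stop measuring someone because of a fall. Procedures for follow-up after stopping an intervention are commonly left to the full protocol, which is not shown. Harm also requires three things that the documents do not establish: the literal reading, actual removals, and a difference in decline between residents removed and residents kept.

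Much of this stands. It makes the shorthand reading plausible and limits the severity. It does not dispose of the point, because the article is not silent here: it states a rule, and the rule concerns study membership. Neither the general measurement schedule nor the intention-to-treat sentence says that a resident taken out after a fall is still measured.

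A reader might be tempted to go further in three ways that the documents do not support:

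- **That confining the review to intervention facilities is itself a fault.** Control residents have no study activity to stop, so reviewing falls in the exposed arm is proper oversight.
- **That the lack of fixed criteria is a fault.** Case-by-case judgement after a fall is normal in frail residents with dementia, and the remedy below keeps it.
- **That fallers will be removed, or that the trial abandons intention-to-treat.** The text allows removal and does not require it, and the commitment to intention-to-treat is explicit.

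**Conclusion.** The point holds as a defect of wording with a possible consequence for the data. As written, the Adverse Events section allows discretionary, unblinded loss of outcomes in the intervention arm only, following a mobility-related event. Whether any loss would occur, how large it would be and which way it would push the result cannot be derived from the documents.

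On the assumed middle case the bias at 6 months is modest: 0.10 to 0.25 stands against a target of 2. It rests on 10% of the arm being removed and on a gap in change of 1 to 2.5 stands. Zero and negative values are equally compatible with the text, so a reader should not infer that the rule favours the intervention. Severity is minor to moderate. The case for acting is that the remedy costs almost nothing and lost outcomes cannot be recovered later.

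**What to change.** Reword the Adverse Events sentence so that, after a fall in an intervention facility, the principal investigator and the facility manager decide whether the sit-to-stand activity continues, is modified or stops. Add that the resident stays in follow-up for the 3- and 6-month outcomes and the monthly falls record, and is analysed in the assigned group, until death or withdrawal of consent.

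The mobility test does make a physical demand: "Residents will be instructed to stand up and sit down as many times as possible until they are asked to stop after 30 seconds". Allow it to be omitted at a visit for clinical safety, under the same rule in both arms, with the reason recorded and the other outcomes still collected. The Functional Independence Measure is obtained by interviewing aides and the QOL-AD is the caregiver version, so neither puts physical strain on a resident who has fallen.

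The cost is one or two sentences, plus slight extra effort to measure residents who have stopped the activity, at visits already planned. Clinical discretion over the activity is unchanged.

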### Knowledge Translation

We have engaged knowledge users from the outset of the project to enhance the likelihood of the uptake and sustainability of the innovation. This is consistent with the two communities theory which emphasizes the importance of bridging the gap between researchers and knowledge users by engaging knowledge users early in the research process [106] and with the literature suggesting that managers attitudes toward an innovation have a strong impact on the adoption of the innovation [107]. The knowledge users and applicants will meet frequently at the beginning of the project and then bimonthly to monitor the progress of the research and provide advice on issues as they inevitably arise. At the end of the study we will host a knowledge translation symposium in which the investigators, the knowledge users, collaborators, and other interested stakeholders will be invited to assess the relevance of the study findings in light of related evidence, the potential impact, and methods to extend the application of the findings. The symposium will provide a forum for a full exchange of ideas in light of the evidence generated from this study and the existing literature. It is in the context of the synthesized evidence that decisions will be made about if and how to integrate the new knowledge into practice and/or policy.

## Discussion

The findings of this study will provide clinically relevant information on the effect of the sit-to-stand functional activity on mobility, function and health-related quality of life among individuals with dementia. Not only will it provide resident-specific information but also how and if health care aides are willing and able to integrate the activity into their daily work with residents; and what might be done to translate these findings into practice to improve care for LTC residents with dementia. The sit-to-stand mobility intervention introduces change at the level of the LTC facility, the health care team, the individual health care aide, and the resident [108].

This project represents an interdisciplinary partnership between knowledge users and new and established investigators, with a focus on maintaining the mobility, function and health-related quality of life of LTC residents. There are several compelling reasons for this study: the widespread prevalence of limited mobility in this population, the rapid decline in mobility after admission to a LTC facility, the critical importance of mobility to quality of life, the increased time (and therefore cost) required to care for residents whose mobility is compromised, and the increased risk of injury for health workers who are providing care for residents unable to stand. The importance of these issues is magnified when considering the increasing number of people living in long-term care facilities and an aging population. Demonstrating a feasible and practical mobility intervention with the potential to improve or maintain functional mobility in frail and vulnerable older Canadians in LTC facilities, and to reduce the risk of injury to direct care providers is a safety, economic and, importantly, a quality of life issue.

## List of Abbreviations

The list of abbreviations contained in this article are as follows: Functional Independence Measure (FIM); Health Utilities Index Mark 2 and 3 (HUI2/3); Health Utilities Index 2 (HUI2); Health Utilities Index 3 (HUI3); long-term care (LTC); Quality of Life - Alzheimer's Disease (QOL-AD); intraclass correlation (ICC); Resident Assessment Instrument 2.0 (RAI 2.0); Depression Rating Scale (DRS); Cognitive Performance Scale (CPS); Changes in Health; End-stage disease Symptoms and Signs Scale (CHESS); Professional Environmental Assessment Protocol (PEAP); Alberta Context Tool (ACT) and Multivariate Analysis of Variance (MANCOVA).
